# Assessment of benefits and risks for the study population

Benefits of participating in the study will be as follows. First, participants will receive free laboratory investigations for soil-transmitted helminthiasis and will be informed in person about their parasitological and clinical results. Second, the infected participants will receive free treatment. Anthelminthic treatment can improve the children’s general health status, including better uptake of nutrition, reduced anemia, and improved growth and cognitive development. Third, at population level, the assessment of a more effective treatment regimen against *T. trichiura* and the early detection of a potential resistance against certain anthelminthic drugs in the frame of this study can lead to appropriate policy recommendations by the Zanzibari government and the WHO and enhance the success of helminth control in Zanzibar and elsewhere.

Risks to participate in the study are due to the side effects that may be associated with anthelminthic drugs and that are generally reported to be mild, transient and self-limiting. Side effects can include fatigue, headache, dizziness, allergic reactions, shivering, abdominal pain, nausea, vomiting, diarrhea or fever.

Medical personal and the drivers of the helminth control team will remain with the treated study participants for one hour after treatment and in case of any acute adverse reaction refer the child to the nearest PHC. The PHCs will remain open for 24 hours on the day of treatment and will be provided with first aid drugs before treatment starts. Children, parents and teachers will be instructed that in case of any adverse reaction they can refer cases to the nearest PHC at day and night time for 24 hours after treatment. In case of any adverse reaction the participant will be treated free of charge.

# Data analysis

The following data will be available for each individual:

Name

Age

Sex

Date of treatment

Drug used

Date of follow up

Parasitological data of first stool examination (double Kato-Katz thick smear)

Parasitological data of second stool examination (double Kato-Katz thick smear and single FLOTAC)

Parasitological data of follow up (2 stool samples with 2 Kato-Katz thick smears per sample and single FLOTAC)

Data on adverse events of treatment after 3 h (acute) and 72 h (solicited).

All data will be entered twice in Microsoft Excel version 10.0 (2002 ® Microsoft Corporation) by local staff in Zanzibar. Datasets will be compared using EpiData version 3.1 (EpiData Association; Odense, Denmark), and discrepancies removed based on the original records by the PhD student ([name]) when back in Switzerland. Statistical analyses will be carried out by the PhD student with JMP version 5.0.1 (SAS Institute; Cary, NC, United States of America). The CR of the treatments and the ERR will be compared for each drug according to the results of either the Kato-Katz or the FLOTAC method or the combination of both methods.

In addition, the frequency and severity of acute and solicited adverse events of the different drug regimens will be compared. The latter analysis will try to seek differential effects according to age, sex and initial parasite load.

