## Objectives

1. Efficacy and safety of albendazole and mebendazole alone and in combination with ivermectin against *T. trichiura*: We will carry out a randomized controlled trial in Kinyasini and Chaani school with the aim to compare the efficacy and safety of a single-dose treatment with albendazole (400 mg), and single-dose treatment with mebendazole (500 mg), a combination treatment with albendazole (400 mg oral dose) plus ivermectin ( 200 µg/kg oral dose) and a combination treatment with mebendazole (500 mg oral dose) plus ivermectin (200 µg/kg oral dose) against *T. trichiura.* Efficacy against other soil-transmitted helminth infections will also be determined to find out the most effective drug regimen to fight trichuriasis in particular and soil-transmitted helminthiasis in general. These results will guide policy recommendations in an appropriate way.

2. Development of resistance against albendazole/mebendazole after several years of mass-administration: To determine the current efficacy of a single-dose treatment with albendazole (400 mg single oral dose) or mebendazole (500 mg single oral dose) against *A. lumbricoides* and hookworm, to compare it to the efficacy of the drugs reported from Zanzibar in the 1990s and to shed light on a potential rise of drug resistance of *A. lumbricoides* and hookworm in Zanzibar within the above mentioned randomized controlled trial in Kinyasini and Chaani school.

3. Comparison of FLOTAC and Kato-Katz method: To compare the performance of the recently developed FLOTAC method with the Kato-Katz method applied by ‘default’ to diagnose soil-transmitted helminth infections under local conditions with the aim to determine their strengths and shortcomings in parasitological surveys and drug efficacy trials.

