## Laboratory procedures

All stool samples will be transferred to the HCLU on the day of collection, and will be examined by experienced laboratory technicians and the PhD-student. At the baseline screening, 2 Kato-Katz thick smears *(*41) from one stool sample per individual using 41.7 mg of stool will be prepared and examined quantitatively for the presence of hookworm eggs after a clearing time of 20-30 min, and subsequently for *A. lumbricoides* and *T. trichiura* eggs. The eggs of *A.* *lumbricoides*, hookworms and *T. trichiura* will be counted and recorded separately. From 250 randomly selected stool samples 1-2 g will be preserved in SAF for subsequent examination with the FLOTAC method *(*54).

From children included into the randomized controlled trial and thus providing another stool sample at the day of treatment and 2 consecutive stool samples for the follow up, a double Kato-Katz thick smear will be prepared and examined. At the days of follow up 1-2 g of stool, from those individuals examined with FLOTAC before treatment and who have been included in the trial, will again be preserved in SAF for subsequent examination with the FLOTAC method. All laboratory investigations will be blinded, e.g. the technicians examining the Kato-Katz slides or FLOTAC apparatus will not be aware of the treatment regimen of the participants. A random sample of 10% of the Kato-Katz thick smears will be re-examined by a Tanzanian senior laboratory technician for quality control.

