**Table 1: Cure rates for *T. trichiura***

**Treatment A (albendazole or mebendazole)**

| **Treatment B**  **(albendazole or mebendazole plus ivermectin)** | 15% | 20% | 30% | 35% | 40% | 45% | 50% | 55% |
| --- | --- | --- | --- | --- | --- | --- | --- | --- |
| 60% | 21 | 27 | 48 | 69 | 106 | 185 | 407 | 1573 |
| 65% | 17 | 21 | 36 | 48 | 69 | 105 | 182 | 395 |
| 70% | 14 | 18 | 28 | 36 | 48 | 67 | 102 | 175 |
| 75% | 12 | 15 | 22 | 27 | 35 | 47 | 65 | 97 |
| 80% | 10 | 12 | 18 | 21 | 27 | 34 | 44 | 61 |
| 85% | 9 | 10 | 14 | 17 | 21 | 25 | 32 | 41 |
| 90% | 8 | 9 | 12 | 14 | 16 | 20 | 24 | 29 |

Based on the given information we estimate the CR of albendazole/mebendazole for *T. trichiura* infections to be between 20% and 45% and the CR of the combination of albendazole/mebendazole plus ivermectin to be between 65% and 80%. Hence, a sample size of at least 105 participants per treatment group is needed for significance analysis.

In the proposed study sites, the prevalence of *T. trichiura* infections is most likely to be above 30% and the compliance is estimated to be around 90%. These assumptions are based on a study performed in Kinyasini and Chaani schools in 2007 where 25.9% of the children were found to be infected with *T. trichiura* after examination of 1 stool sample and 47.9% after examination of 3 stool samples with the Kato-Katz method and where the compliance to submit 1-3 stool samples was >85%. In view of the required number of cases per group, and allocating for patients lost to follow-up, at least 2000 subjects would have to be screened so that 500-600 infected individuals infected with *T. trichiura* can enter the trial (see Appendix 5).

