**Week 9 and 10**

- Distribute labelled stool container to all children treated in the randomized trial

- Collect filled stool containers from all children and transport them to the laboratory, distribute a labelled new stool container for every one that was collected until each child submitted 2 stool samples after treatment

- Prepare 2 Kato-Katz smears from each stool sample and examine as described beyond until 2 consecutive stool samples from all children included into the trial were examined with the Kato-Katz method

- Preserve 1 g of 1 stool sample in a labelled container with 10ml SAF from the sub-sample of children randomly selected to be examined with FLOTAC and which finally entered the trial

- Inform participants in person about the parasitological diagnosis

- Treatment of all participating school-children free of charge with albendazole by members of the national helminth control team

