**Appendix 5: Overview participation**

| **ID** | **Name** | **Sex** | **Age** | **Sample A (No. K-K)** | **RCT**  **(Yes/No)** | **Sample B (No. K-K)** | **Sample A (FLOTAC)** | **Treatment**  **(Alb, Meb, Alb+Ivm, Meb+Ivm)** | **Sample C (No. K-K)** | **Sample D (No. K-K)** | **Sample C/D (FLOTAC)** |
| --- | --- | --- | --- | --- | --- | --- | --- | --- | --- | --- | --- |
| **0001** |  |  |  |  |  |  |  |  |  |  |  |
| **0002** |  |  |  |  |  |  |  |  |  |  |  |
| **0003** |  |  |  |  |  |  |  |  |  |  |  |
| **0004** |  |  |  |  |  |  |  |  |  |  |  |
| **0005** |  |  |  |  |  |  |  |  |  |  |  |
| **0006** |  |  |  |  |  |  |  |  |  |  |  |
| **0007** |  |  |  |  |  |  |  |  |  |  |  |
| **0008** |  |  |  |  |  |  |  |  |  |  |  |
| **0009** |  |  |  |  |  |  |  |  |  |  |  |
| **0010** |  |  |  |  |  |  |  |  |  |  |  |
| **0011** |  |  |  |  |  |  |  |  |  |  |  |

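### At follow-up, Kato-Katz is read on two stools and FLOTAC on one unspecified stool, so the cure-rate comparison by method mixes method with number of stools

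*Combined protocol and SAP*

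**What the plan says.** Objective 3 is "To compare the performance of the recently developed FLOTAC method with the Kato-Katz method", both for parasitological surveys and for drug efficacy trials.

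Follow-up sampling is described in four places:
- **Laboratory procedures:** trial children give "2 consecutive stool samples for the follow up, a double Kato-Katz thick smear will be prepared and examined".
- **Data analysis:** the data available are "Parasitological data of follow up (2 stool samples with 2 Kato-Katz thick smears per sample and single FLOTAC".
- **Appendix 3, Week 9 and 10:** for the FLOTAC sub-sample, "Preserve 1 g of 1 stool sample in a labelled container with 10ml SAF".
- **Appendix 5:** Kato-Katz has separate columns for Samples C and D. FLOTAC has one column, headed "Sample C/D (FLOTAC".

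On the analysis, the Data analysis section says "The CR of the treatments and the ERR will be compared for each drug according to the results of either the Kato-Katz or the FLOTAC". A result from the two techniques together is also foreseen. The section does not say which Kato-Katz smears enter that comparison.

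Before treatment, Laboratory procedures, Appendix 3 (Week 2 to 5) and Appendix 5 all place FLOTAC on the screening stool (Sample A) of about 250 randomly chosen children. The Data analysis section instead lists the pre-treatment FLOTAC under the second stool examination.

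**The concern.** *T. trichiura* detection in these schools depends strongly on how many stools are examined. The Sample size section reports 25.9% of children "infected with *T. trichiura* after examination of 1 stool sample and 47.9% after examination of 3 stool samples" by Kato-Katz. A child still infected after treatment has two chances to be found by Kato-Katz, on different days, but only one by FLOTAC.

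A missed infection counts as a cure, so the method with fewer stools tends to show the higher CR and to look less sensitive. The imbalance favours Kato-Katz whatever the true merit of FLOTAC. The combined result has the same flaw, because it would include infections seen only in a stool that FLOTAC never received.

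A later repair depends on knowing which stool was aliquoted. If the form does not record C or D, a same-stool analysis at follow-up may not be recoverable.

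**Working it through.** The plan states no power or sample size for the method comparison, so there is no planned figure to reproduce. The check asks what its 2007 figures imply about a second stool.

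**Inputs.** Kato-Katz positivity of 25.9% (one stool) and 47.9% (three stools), from Sample size; 41.7 mg per smear, from Laboratory procedures; FLOTAC transfers 5 ml of a 6 ml suspension of 1 g stool, from Appendix 3. The prevalence and losses in step 5 come from the Appendix 8 flowchart.

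**1. Equal, independent detection s per stool in infected children.**
- (1 − (1 − s)³)/s = 3 − 3s + s² = 47.9/25.9 = 1.849
- s = [3 − √(9 − 4(3 − 1.849))]/2 = 0.451
- Implied true prevalence: 0.259/0.451 = 57.4%. Check: 0.574 × (1 − 0.549³) = 47.9%.
- Two stools: 1 − 0.549² = 69.9%. Ratio to one stool: 0.699/0.451 = 1.55.

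**2. Detection varying between children.** The second stool adds at least as many positives as the third, so two-stool positivity is at least 25.9 + (47.9 − 25.9)/2 = 36.9%, a ratio of 36.9/25.9 = 1.42. The equal-detection case is the maximum: 40.1%, ratio 1.55. Beta-binomial values inside these bounds are 40.3% and 61.9% (one and two stools) at intra-child correlation 0.1, and 33.9% and 51.9% at 0.2; both ratios are about 1.53.

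**3. Effect on CR.** Apparent CR = 1 − (proportion still infected) × (detection), assuming no false positives. For illustration, assume that 55% are still infected and that FLOTAC detects 60% on one stool; neither figure is in the documents. FLOTAC CR is then 1 − 0.55 × 0.60 = 67.0%.

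| Intra-child correlation | Kato-Katz CR, same stool | Kato-Katz CR, two stools | FLOTAC CR | FLOTAC/Kato-Katz detection, same stool | Ranking reversed? |
|---|---|---|---|---|---|
| 0 | 75.2% | 61.5% | 67.0% | 0.60/0.451 = 1.33 | Yes |
| 0.1 | 77.8% | 66.0% | 67.0% | 0.60/0.403 = 1.49 | Barely; near tie |
| 0.2 | 81.4% | 71.5% | 67.0% | 0.60/0.339 = 1.77 | No; gap narrows |

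On the same stool FLOTAC finds more failures in every row. With two Kato-Katz stools, its lead shrinks from 14.4 to 4.5 points in the last row and is lost in the first two.

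**4. Stool mass.** A double smear uses 2 × 41.7 = 83.4 mg and four smears 166.8 mg. FLOTAC reads about 5/6 g = 833 mg, ten times a double smear. As an assumed model, take a negative binomial egg count per stool with day-to-day shape k and s = 0.451. FLOTAC detection is 1 − (1 + 10·r·x)^(−k), where x = (1 − s)^(−1/k) − 1 and r is FLOTAC's egg recovery relative to Kato-Katz. It falls below 69.9%, so that the ranking reverses, when k is below about 0.27 (r = 1), 0.43 (r = 0.5) or 1.5 (r = 0.25).

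**5. Size of the sub-sample.** With 250 FLOTAC samples, 30% prevalence and the flowchart losses, 250 × 0.30 × 103/135 ≈ 57 infected children have follow-up data. At 25% prevalence it is about 48.

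**The case against.** **The plan does not say that all four smears enter the comparison.** The follow-up entry belongs to a list of available data, and the sentence on CR could mean comparing treatments under each method in turn. That is fair. The defect is a missing rule, not a stated wrong choice. But the plain reading uses all available data per method, and nothing excludes it.

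**FLOTAC might be run on both stools.** Laboratory procedures speaks of preserving stool at the days of follow-up, in the plural. The Data analysis section, Appendix 3 and Appendix 5 all provide for one FLOTAC result.

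**FLOTAC's larger stool mass may outweigh the second stool.** It may. With equal egg recovery, reversal needs strong day-to-day variation. This limits the claim of reversal but does not remove the confounding.

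**The 2007 figures come from a survey.** They are not post-treatment stools, and the smears per stool are not stated. The 1.4 to 1.55 range is therefore indicative.

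**The sub-sample is small.** In the first row of the table the planned gap is 5.5 points, about 3 of 57 children. This weakens any conclusion about ranking, however the comparison is made.

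**Two Kato-Katz stools against one FLOTAC is a legitimate operational question.** It is, if labelled as such. It does not show which technique performs better on the same material.

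**Conclusion.** The point holds for the follow-up, drug-efficacy part of Objective 3. As written, the CR comparison by method confounds technique with number of stools, in favour of Kato-Katz. The second stool is worth a factor of about 1.4 to 1.55 in Kato-Katz detection, if the 2007 survey figures carry over to post-treatment stools and stools are independent given the child.

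A reader might go further in three ways that the documents do not support:
- **That the ranking will reverse and Objective 3 will be answered wrongly.** Reversal requires FLOTAC's same-stool advantage to lie below about 1.4 to 1.55. The Background expects FLOTAC to be more sensitive but gives no figure. Above that range its advantage is only understated.
- **That the baseline comparison suffers equally.** Three places put FLOTAC on Sample A, which also has a double Kato-Katz smear, so a same-stool comparison is already possible there.
- **That the egg reduction rate (ERR) is biased in a known direction.** No such bias has been shown; extra smears mainly make a mean count more precise.

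The primary Kato-Katz efficacy outcome is unaffected.

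**What to change.** 1. **Data analysis:** state that the main FLOTAC-versus-Kato-Katz comparison, and the result combining both methods, uses only the double smear from the stool aliquoted for FLOTAC. Analyse it as paired data within child.
2. **Appendix 3 (Week 9 and 10) and Appendix 5:** fix the follow-up FLOTAC aliquot to Sample C, or at least record for each child whether C or D was used.
3. **Pre-treatment FLOTAC:** reconcile the Data analysis section, which lists it with the second stool examination, with Laboratory procedures, Appendix 3 and Appendix 5, which place it on Sample A.
4. **Four-smear result:** report the two-stool Kato-Katz CR separately as the primary efficacy outcome and, if wanted, against single FLOTAC as a labelled operational comparison.

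The cost is a few sentences and one column heading, with no extra samples or readings. The Kato-Katz CR in the method comparison will differ from the primary CR, so a footnote is needed to explain why.

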# Background

## Helminth infections

Worm infections remain a major public health problem, particularly in tropical and subtropical regions, primarily affecting socio-economically deprived populations. It is estimated that over a third of the world’s population is currently infected with helminths (‘parasitic worms’) *(1,* 2). This proposal will focus on soil-transmitted helminths, which are estimated to infect more than a billion people globally and are highly prevalent across sub-Saharan Africa *(2,* 3).

Soil-transmitted helminths are intestinal parasitic worms. Humans are the definitive host. These parasites are rampant in areas where hygienic conditions are poor and environmental features are adequate (e.g. high temperatures, sufficient soil moisture). Infections frequently cause chronic and debilitating disease, mainly in infants, pre-school and school-aged children and pregnant women *(2, 4,* 5).

Humans become infected through ingestion of parasite eggs or penetration of infectious larvae through the skin (2). The adult soil-transmitted helminths can live for years in the human gastrointestinal tract. The most common soil-transmitted helminths are the large roundworm (*Ascaris lumbricoides*), the whipworm (*Trichuris trichiura*), and the hookworms (*Ancylostoma duodenale* and *Necator americanus*).

Morbidity due to soil-transmitted helminth infection and the rate of transmission are related to the number of worms harboured by the host (6). Generally, infections with soil-transmitted helminths have a negative impact on pregnancy and birth outcomes, hamper children’s cognitive and physical development, result in reduced work capacity, and therefore compromise the social and economic development of communities and entire nations *(3, 7,* 8). Recent estimates suggest that globally 807-1221 million people are infected with *A. lumbricoides*, 604-795 million with *T. trichiura*, and 576-740 million with hookworm *(1,* 2). Infections with multiple helminth species are common *(9,* 10). In Africa, it is currently estimated that 44% of soil-transmitted helminth infections are concentrated in just four countries, namely Nigeria, Democratic Republic of Congo, South Africa and Tanzania *(*11). The global burden of soil-transmitted helminthiasis is estimated at 39 million disability-adjusted live years (DALYs), hence similar to the global burden owing to malaria or tuberculosis *(7,* 12).

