## Safety of the benzimidazoles

On Zanzibar, multiple studies on the efficacy of mebendazole, albendazole, ivermectin and albendazole plus ivermectin have been conducted *(18-20, 45, 46, 48, 50,* 51). Actively assessed, no severe side effects were recorded for albendazole or ivermectin in a trial conducted in Unguja in 1994, and mild side effectswere of transient nature for both treatments *(*18). Although not actively assessed, no adverse events were reported after mebendazole treatment in the week following the administration of anthelminthics in Pemba *(*48). No severe adverse reactions were reported from a trial conducted in Zanzibar in 2006 to assess the safety of triple drug co-administration (albendazole plus ivermectin plus praziquantel) *(*19). The combined treatment of albendazole and ivermectin is successfully and safely applied to treat the Zanzibari population since 2001 in the frame of the GPELF *(*20). In general, the side effects of albendazole and mebendazole, at the dosage recommended for deworming, have been described as negligible and self-limiting *(*52). However, even if the single applications of albendazole, mebendazole and ivermectin are reported to be safe, to our knowledge, there are no reports on the combined treatment of mebendazole and ivermectin. Hence, the safety of the latter drug combination needs to be confirmed.

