1. Single-dose albendazole group; children will receive one tablet of albendazole (400 mg) and a placebo resembling ivermectin (number of tablet according to weight).
2. Mebendazole group; children will receive a single dose of mebendazole (500 mg) and a placebo resembling ivermectin (number of tablet according to weight).
3. Albendazole plus ivermectin group; children will receive one tablet of albendazole (400 mg) plus ivermectin tablets according to their weight (200 µg/kg).
4. Mebendazole plus ivermectin group; children will receive one tablet of mebendazole (500 mg) plus ivermectin tablets according to their weight (200 µg/kg).

The participants will be asked to swallow the drugs with clean water and the health worker administering the drugs will check that the tablets have been swallowed by looking into the mouth and under the tongue. During the entire treatment phase and for one additional hour, a clinician will be present for supervising drug intake, monitoring and registering acute adverse events of the four drug regimens and to provide medical assistance where necessary. The medical assistant will be provided with a complete list of possible adverse events of the respective drug. In case of adverse events, appropriate medical action will be taken, e.g. administration of drugs for relief.

The children will be kept under medical supervision for one hour after treatment. The staff of the Public Health Centres (PHC) located nearest to the two schools (Upenja and Chaani) will be informed and undergo a pharmacovigilance training in the week before treatment. Additionally, the PHCs will be provided with first aid drugs and will remain open for 24 hours on the day of treatment. Children, parents and teacher will be informed that in case of any adverse reaction they can refer cases to the PHC at day and night time for 24 hours. Forty eight hours after treatment, solicited adverse events due to the treatment will be assessed by a previously tested questionnaire (see Appendix 3). The onset and duration of the side effects will be recorded and graded as follows:

- *mild:* present but not requiring any interference;
- *moderate:* (1) present and requiring medication for symptomatic relief as requested by the affected people or (2) present and interfering with normal daily activities; and
- *severe:* present and required medical intervention beyond symptomatic relief.

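### Without a pre-dose symptom record or a rule for complaints that began before treatment, adverse-event rates compared across initial parasite load could not separate worm-related complaints from drug effects.

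*Combined protocol and SAP*

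**What the plan says.** **Timing of symptom recording.** Under Field procedures, children are watched for one hour after treatment, and then: "Forty eight hours after treatment, solicited adverse events due to the treatment will be assessed by a previously tested questionnaire". The same section adds: "The onset and duration of the side effects will be recorded and graded as follows". The per-child data list under Data analysis has a single safety entry: "Data on adverse events of treatment after 3 h (acute) and 72 h (solicited". Appendix 3 (Detailed field and laboratory procedures) has monitoring for 3 hours and again at 3 days. These times differ (1 h or 3 h; 48 h or 72 h/3 days), but all of them fall after dosing.

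**Before dosing.** The only clinical contact described is an examination for eligibility. It excludes children with fever, acute illness, pregnancy or severe neurological or liver disorder. Neither the data list, the weekly schedule in Appendix 3 nor the participation form in Appendix 5 contains a symptom item from before treatment.

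**Analysis.** Data analysis states that "the frequency and severity of acute and solicited adverse events of the different drug regimens will be compared", and continues: "The latter analysis will try to seek differential effects according to age, sex and initial parasite load". No model is given, and treatment-emergent events are not defined.

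**Context.** The Background says: "Morbidity due to soil-transmitted helminth infection and the rate of transmission are related to the number of worms harboured by the host". On mebendazole plus ivermectin, the section on the safety of the benzimidazoles finds no earlier reports and concludes: "Hence, the safety of the latter drug combination needs to be confirmed". All four arms receive albendazole or mebendazole; the placebo stands in for ivermectin only.

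**The concern.** The side effects listed in the benefit and risk section, such as abdominal pain, nausea, diarrhoea, headache and fatigue, are non-specific. A child with intestinal worms may have some of them before swallowing any tablet. Every participant is infected and every arm gets an active drug, so no group in the trial shows how often these complaints occur without treatment.

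Two results are exposed. The first is any comparison of event rates between children with high and low initial load. Load is not randomised, so a difference in background complaints would look like a difference in drug tolerability. The second is the absolute event rate of mebendazole plus ivermectin, the combination whose safety the trial is meant to establish; it would include complaints that have nothing to do with the drugs. The comparison between randomised arms is affected in a milder way: background is balanced, but it dilutes a true difference.

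**Working it through.** **The plan's own figure.** The documents give no rate, sample size or power for adverse events. The 105 per group in the Sample size section is for cure rates of 45% v 65%, and it reproduces: 7.85 × (0.45×0.55 + 0.65×0.35)/0.20² + 2/0.20 + 2 = 93.2 + 10 + 2 = 105.2. It does not bear on this point.

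**Model.** Treat each child as having a complaint or not. Let b be the share with a background complaint before dosing, and r the risk that the drug causes one in a child who has none. The share with a complaint recorded after dosing is b + (1 − b) × r. All values of b and r below are assumptions.

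**Across load strata, with r the same at every load (true ratio 1.0):**

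| Background, low v high load | r | Recorded, low v high | Apparent ratio |
|---|---|---|---|
| 10% v 10% | 10% | 19.0% v 19.0% | 1.00 |
| 5% v 10% | 10% | 14.5% v 19.0% | 1.31 |
| 10% v 20% | 10% | 19.0% v 28.0% | 1.47 |
| 10% v 30% | 5% | 14.5% v 33.5% | 2.31 |

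For example, 0.10 + 0.90×0.10 = 0.19 and 0.20 + 0.80×0.10 = 0.28; 0.28/0.19 = 1.47. The false gradient comes entirely from the assumed difference in background; with no such difference it disappears.

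**With a pre-dose record (10% v 20% row).** New complaints as a share of all children are 0.90×0.10 = 9% v 0.80×0.10 = 8%. As a share of children free of the complaint before dosing, they are 10% v 10%. The denominator matters: only the second version recovers the equal drug risk.

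**Between randomised arms.** Assume drug risks of 5% and 15%, the same background in both arms, and 114 treated children per arm (Appendix 8). Power is for a two-sided 5% two-proportion z-test (pooled variance under the null, separate variances under the alternative).

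| Background | Recorded rates | Difference | Ratio | Power |
|---|---|---|---|---|
| 0% | 5.0% v 15.0% | 10.0 points | 3.00 | 71% |
| 10% | 14.5% v 23.5% | 9.0 points | 1.62 | 41% |
| 20% | 24.0% v 32.0% | 8.0 points | 1.33 | 27% |
| 30% | 33.5% v 40.5% | 7.0 points | 1.21 | 19% |

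If the two drug risks are equal, the recorded rates are equal at any background, so no false difference arises.

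**Regimen difference by load.** Read the second table as load strata: with 10% background at low load and 20% at high load, the arm ratio moves from 1.62 to 1.33 and the difference from 9 to 8 points, although the drug risks are unchanged. Even under this reading, unequal background disturbs the result, modestly on the difference scale and more on the ratio scale.

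**The case against.** A reader might infer that the plan is bound to count worm complaints as drug effects, and that the load analysis must show a gradient. The documents do not support that.

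- **Onset is recorded.** A complaint that began before dosing could be set aside on that basis. What is missing is a rule to do so. It would also rest on children's recall two or three days later, and onset alone does not show whether an existing complaint got worse.
- **The questionnaire cannot be seen.** The content of Appendix 4 is a figure missing from the copy reviewed. It may ask about earlier symptoms, so its absence proves nothing either way. The point rests on the visible text: the data list has no such variable and no rule uses one.
- **The sentence is ambiguous.** It follows a comparison of randomised regimens and may mean that the regimen difference is to be examined by load. Background is then balanced between arms within each stratum and mainly dilutes. The confounding described here arises when event rates are compared across strata, within arms or pooled. The plan does not say which is intended.
- **The gradient is assumed.** The Background ties morbidity to worm number, but the effects it goes on to describe are on pregnancy, child development and work capacity, not short-lived headache or nausea. It also reports few heavy infections even before the control programme, and a decline in intensities since. For age, nothing in the documents points to a gradient.
- **The stakes are limited.** The load analysis is exploratory in wording, acutely ill children are excluded, mebendazole plus placebo is a direct comparator for mebendazole plus ivermectin, and an overstated absolute rate errs on the cautious side.

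All of this narrows the point. None of it supplies a pre-dose record or a rule for complaints that preceded treatment.

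**Conclusion.** The point holds in conditional form. As written, the plan has no means of separating existing complaints from new ones other than recalled onset, for which it states no rule. If worm-related complaints rise with load, event rates compared across load could not be read as drug effects, and the absolute rate for mebendazole plus ivermectin would include background.

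The size cannot be fixed from the documents. Assumed backgrounds of 5% v 10% or 10% v 20%, with an equal 10% drug risk, give apparent load ratios of 1.31 and 1.47; equal backgrounds give 1.0. A reader might also infer that the randomised comparison is biased. It is not: background lowers its power and creates no false difference between arms.

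This is a worthwhile, inexpensive improvement to the safety analysis rather than a flaw in the trial's main comparison. It is best made before the first treatment day, because a pre-dose record cannot be reliably reconstructed later.

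**What to change.** 1. On the day of treatment, before dosing, ask each child the same symptom questions as in the post-dose questionnaire. The child already hands in stool, is weighed and is seen by medical personnel that day.
2. Add this record to the per-child list under Data analysis.
3. Define an adverse event as a symptom that is new, or worse than before dosing. Use this definition for the arm comparison and for the age, sex and load analyses.
4. For each symptom, also report new onset among children who were free of it before dosing.
5. State whether the load analysis compares regimens within load strata or event rates across strata, and on which scale.
6. Reconcile the observation times, which differ between Field procedures on the one hand and Data analysis and Appendix 3 on the other.

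The cost is a few minutes per child, one short form and its data entry, with staff already present. Asking beforehand may slightly prompt later reporting, but equally in all arms. The change reduces the problem without removing it: worm-related complaints that start after dosing would still be counted, and could still vary with load.
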